## 7. Ethical Considerations

The study will be undertaken according to the principles of ICH Good Clinical Practice (GCP), and all relevant ethics and governance processes, including the HRA approvals. All of the research team will be GCP compliant.

Before the study starts, REC approval via IRAS, HRA approval and University of Hertfordshire local ethics review approval will be sought. NHS Research and Development team at the East and North Hertfordshire Trust, Guys and St Thomas' NHS Trust and Luton and Dunstable NHS Trust will need to review and accept the study. NIHR Portfolio status will be sought.

The CI or PI at the lead site (ENHT) will complete an annual progress report to be submitted to the REC and each NHS R&D department.

## 8. Quality Assurance and Control

### 8.2. Risk Assessment

This study is determined as low risk; the rights and safety of participants will be upheld throughout. All participants will perform a warm up and cool down for every WBV session, however muscle soreness has been identified as a risk factor. WBV is low intensity and undertaken with 1:1 supervision, which with the warm/cool down reduces this risk. The research assistant will be first aid trained, and there is a defibrillator on site. All risks associated with the study have been assessed using the University of Hertfordshire's Life and Medical Sciences (LMS) risk assessment form.

The project concept is being supported by an established and experienced Trial Management Group and the Lead PI is being supported and mentored to run the trial via the CI who has extensive experience in this style of research.

The Trial is supported by the UH CTSN in terms of QC and QA to ensure the study is performed and data generated/documented and reported in compliance with the principles of GCP, they are also reportable to regarding study recruitment rates.

### 8.3. Monitoring

The site PIs will be responsible for reviewing participant medical data, the CI, Lead PI and Research Assistant will be responsible for reviewing data errors and missing data on the database. Site visits will occur annually by the CI/delegated responsible person. As the participants will be attending the University of Hertfordshire site, the Lead PI and Research Assistant will be monitoring the study at site level. The Study will be subject to monitoring audits as per the University of Hertfordshire CTSN.

### 8.4. Study Oversight

#### 8.4.3. Trial Management Group

The study is overseen by the Trials Management Group, consisting of the CI (and Exercise Science Specialist), the Lead PI (Gastroenterologist and Researcher), the Senior Research Assistant, the Statistician, Patient Participant, Immunologist, Sports Psychologist (qualitative research specialist), PI/Gastroenterologist and Bio-Engineer. They meet quarterly to input into the design and delivery of the trial, ensure recruitment is progressing and ensure the study is running to target and after the study period support the dissemination programme of the results. The CTSN will also have oversight of the study.

## 9. Public and Patient Involvement

PPI has been integral to the design of the study and each of the patient facing documents have had input from the Patient Participant on the TMG. The CI has lived experience of Crohn's so brings this aspect also to the study. 86% of patient volunteers who undertook a survey regarding whole body vibration exercise state they would be willing to take part in a study regarding this. Tolerability has also been assessed with a pilot study of WBV in Crohn's volunteers. These have moulded the current study design.

## 10. Protocol Compliance

The CI will ensure that the trial is conducted in compliance with the principles of the Declaration of Helsinki (1996), and in accordance with all applicable regulatory requirements including but not limited to the Research Governance Framework, Trust and Research Office policies and procedures and any subsequent amendments.

The sponsor will maintain a log of the non-compliances to ascertain if there are any trends developing which to be escalated. The sponsor will assess the non-compliances and action a timeframe in which they need to be dealt with. Each action will be given a different timeframe dependent on the severity. If the actions are not dealt with accordingly, the R&D Office will agree an appropriate action, including an on-site audit.

## 11. Data Protection and Participant Confidentiality

### Confidentiality

The Investigator has a responsibility to ensure that participant anonymity is protected and maintained. They must also ensure that their identities are protected from any unauthorised parties. Information with regards to study participants will be kept confidential and managed in accordance with the Data Protection Act, NHS Caldicott Guardian, The Research Governance Framework for Health and Social Care and Research Ethics Committee Approval.

Patient identifiable information shared across the research team is limited to name, email address and phone number. Hospital number and date of birth is collected on CRFs at the NHS site - but pseudo-anonymised with a patient research number. Only members of the research team will have access to this information.

The CI is custodian of the data.

The participants can withdraw at any stage, but any data collected up until the point of the withdrawal will still be used within the study. The patients will be asked for a preference of contact details and can withdraw this at anytime by informing the research team.

All data will be anonymised within any publications or dissemination of findings. The CI is the data controller and the research teams both on NHS site and at the University of Hertfordshire are the data handlers. The responsibility for data quality is described above. DPIAs will be completed for each NHS site with the University of Hertfordshire.

**Case Report Form (CRF)** forms are visit specific and are completed by the research assistant or member of the research team undertaking that particular visit parameter.

The Baseline and exit CRFs will record the data as described above

The WBV CRFs will confirm the number of WBV 60 seconds undertaken and confirmation of the lifestyle education delivery.

It will also confirm any AEs during the WBV intervention.

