#### 4. Trial/Study Procedures

##### 4.1. Trial/Study Setup

The trial setup will proceed as follows (further details in GANTT chart below):

1. Obtain ethical approval, set up trial steering group and begin recruiting (Months 1-3)
  - a. Sign contracts
  - b. Set up trial governance
  - c. Collate lifestyle education information from publicly available Crohn's and Colitis UK Patient information.
2. Recruit and enrol 55-60 participants (Months 4-12)
  - a. Undertake baseline assessments
  - b. Deliver exercise intervention and lifestyle education programme
  - c. Undertake post intervention assessments and participant interviews
3. Complete recruitment (12-27 months)
  - a. Finish recruiting at 27 months (168 participants in total)
  - b. Finish baseline assessments
4. Complete measurements of secondary outcome measures (28-31 months)
  - a. Complete interviews
5. Analysis of data, dissemination and report writing (32 – 36 months)
  - a. Bloods analysis
  - b. Interview analysis
  - c. Data analysis
  - d. Dissemination – organising workshops to disseminate results

[figure not shown]

Caption

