## 4.4. Allocation/Randomisation

### 4.4.1. Randomisation Procedures

Once screening procedures have confirmed the participant's eligibility to enter the trial/study and the participant has provided informed consent, the process of randomisation can commence.

The participants will be 1:1 randomised using REDCAP (an automated process) after screening confirmation and consent, this process is immediate and will be done whilst the participant is undergoing baseline measurements (as defined below). This is done by the member of the research team undertaking the screening and consent (e.g. the research assistant). As the trial cannot be blinded there is no code break. Once the participant has been successfully randomised in VECTOR, the enrolment of this participant must be documented within an enrolment log.

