### 5. Safety

Adverse event reporting will be conducted in accordance with the Sponsor's Adverse Event Reporting Procedures. A clinical co-investigator will be responsible for determining the causality and seriousness of adverse events, as well as all non-serious adverse events that are either deemed to be related to participation in the research or result in withdrawal from the WBV programme or study.

Serious adverse events are defined as any untoward medical occurrence that results in one of the following criteria: results in death; is life threatening; requires unplanned or prolonged hospitalization; results in persistent or significant disability or incapacity, or; results in a congenital abnormality or birth defect. Non-serious events are defined as any untoward medical occurrence that does not fulfil any of the serious adverse event criteria.

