## 6.3. Data Analysis

All analyses of the intervention-based data will be performed on an intention to treat basis.

To determine the effects of the intervention on all of the outcome measures, differences in the changes from baseline to after the 6 week intervention between the two groups will be examined using linear mixed effects models with group modelled as a fixed factor and random intercepts by participants adopted. For linear mixed models the mean difference between groups in change from baseline to after the 6 week intervention and 95% confidence intervals of the difference will be presented.

Effect sizes and their associated 95% confidence intervals will also be calculated for the changes from baseline to after the 6 weeks of intervention between the two groups, using Cohen's d, in accordance with McGough, & Faraone. Cohen's d values will be interpreted as 0.2 = small, 0.5 = medium, and 0.8 = large .

Analyses will be conducted in SPSS (IBM, SPSS, V28). The flow of participants through each stage of the trial will be presented in a CONSORT diagram. Descriptive statistics of means and standard deviations will be used to characterise the groups at baseline and differences between the two groups

will be presented in the form of an unadjusted mean difference for continuous outcomes, with their associated 95% confidence intervals.

In addition, Pearson chi-square tests of independence will be utilized to undertake bivariate crosstabulation comparisons between the two trial groups to test differences in the number lost to follow-up and the number of adverse outcomes in each group. Chi-squared probability values will be calculated using Monte Carlo simulation. All statistical analyses will be conducted using SPSS v28 (IBM, SPSS), with statistical significance accepted at the  $P \leq 0.05$  level.

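### The only adverse-event form described belongs to the WBV arm, yet adverse outcomes are compared between arms by chi-square, so a WBV excess may partly reflect closer ascertainment

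*Protocol*

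**What the plan says.** - **Forms (Section 11, Case Report Form paragraph).** Forms are specific to the visit, and three kinds are described: baseline, exit and WBV session. Of the WBV form the protocol says: "It will also confirm any AEs during the WBV intervention". Of the other two it says: "The Baseline and exit CRFs will record the data as described above".
- **What those two forms refer back to (Sections 4.5, 4.7 and 6.1).** The baseline list, the closing-visit list and the list of data to be collected contain no adverse-event item.
- **Contacts (Section 4.6).** The WBV arm attends 18 intervention visits in person. The control arm has one individual Zoom session a week for six weeks, and no form is described for it.
- **Safety (Section 5).** "Adverse event reporting will be conducted in accordance with the Sponsor's Adverse Event Reporting Procedures". This is not limited to one arm, and neither is the definition of a serious event. Non-serious events are singled out if they are related to taking part or "result in withdrawal from the WBV programme or study".
- **Analysis (Section 6.3).** Pearson chi-square tests with Monte Carlo probability values will "test differences in the number lost to follow-up and the number of adverse outcomes in each group". Significance is set at P ≤ 0.05.

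**The concern.** A between-arm test of adverse outcomes is interpretable only if both arms had the same chance of having an event noticed and written down. As described, one arm is seen face to face three times a week by staff holding a form that covers adverse events. The other has a weekly video call with no described form.

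Serious events should reach the record in either arm. Mild events depend most on someone being there to note them, and Section 8.2 itself names muscle soreness as a risk. One of the withdrawal routes in Section 5, leaving the WBV programme, can arise only in the WBV arm.

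At stake is the safety conclusion of a trial that the Introduction presents as the first of WBV in Crohn's disease. If the chi-square is significant, the data as collected could not separate a real effect of WBV from closer observation. No analysis plan can recover control-arm events that were never elicited.

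**Working it through.** The protocol gives no adverse-event rate and no safety sample size, so there is no stated figure to reproduce. The check has two parts.

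**1. Collection set against analysis**

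| | WBV arm | Control arm |
|---|---|---|
| Contacts during the six weeks | 3 × 6 = 18, in person | 1 × 6 = 6, by Zoom |
| Session form that captures adverse events | Yes | None described |
| Adverse-event item in the baseline, exit or data lists | None | None |
| Sponsor's reporting procedures (Section 5) | Apply | Apply |
| Entered in the chi-square (Section 6.3) | Yes | Yes |

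The two columns differ in form and in number of contacts, and then enter one test on equal terms.

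**2. How much unequal capture could matter**

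Inputs from the protocol:
- total sample: "Finish recruiting at 27 months (168 participants in total" (Section 4.1);
- allocation: "The participants will be 1:1 randomised using REDCAP" (Section 4.4.1), so 168 / 2 = 84 per arm;
- significance level 0.05 (Section 6.3).

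Assumed inputs, none of them in the protocol:
- the same true risk *p* of at least one event in both arms, taken as 10%, 20% and 30%;
- every affected WBV participant is recorded;
- a share *s* of affected control participants is recorded;
- no dropout.

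With *X* and *Y* recorded participants in the WBV and control arms and *n* = 84 in each, the Pearson statistic is

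χ² = 2*n*(*X* − *Y*)² / [(*X* + *Y*)(2*n* − *X* − *Y*)],

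with *X* ~ Binomial(84, *p*) and *Y* ~ Binomial(84, *ps*). The null is rejected when χ² is at least 3.84.

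At the expected counts for *p* = 20% and *s* = 50%, *X* = 16.8 and *Y* = 8.4. Then χ² = 168 × 8.4² / (25.2 × 142.8) = 3.29, a little under the critical value, which fits a rejection rate somewhat below one half. For *p* = 30% and *s* = 50%, the counts are 25.2 and 12.6, and χ² = 168 × 12.6² / (37.8 × 130.2) = 5.42.

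Summing the exact binomial probabilities over all pairs (*X*, *Y*) that reject gives the chance of a significant result when the true risks are equal:

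| True risk in both arms | *s* = 100% | *s* = 75% | *s* = 70% | *s* = 50% |
|---|---|---|---|---|
| 10% | 5.0% | 8.5% | 10.3% | 22.2% |
| 20% | 5.1% | 13.7% | 17.9% | 44.4% |
| 30% | 5.1% | 19.8% | 26.9% | 65.7% |

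With equal capture, about half of the 5% falls against WBV. At 75% capture or below, nearly all of the rejections do: at 20% risk and 70% capture, 17.7 of the 17.9 percentage points. The calculation uses the asymptotic critical value, whereas the plan uses Monte Carlo probability values, which may shift these figures somewhat.

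**The case against.** **Section 5 covers the whole trial.** A reader might infer that control-arm events go unrecorded. The protocol does not support that. The sponsor's procedures apply to both arms, they are not shown, and they may set out control-arm collection. The data list in Section 6.1 does not settle it either: it omits adverse events for both arms, and also omits the number of vibration bouts that the WBV form records, so it is not exhaustive. What stands is narrower. The protocol describes no control-arm form, question or time point, and a reporting procedure is not the same as a matched schedule of asking.

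**The size is assumed.** No event rate or capture share is stated, and weekly one-to-one Zoom contact plus an exit visit may catch most events. This is right, and the percentages are illustrative only. The direction of the bias is not in doubt if capture is lower in the control arm.

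**Some excess under WBV could be real.** Muscle soreness is an expected effect of the exercise. A reader might infer that WBV is bound to look less safe through ascertainment alone. The documents support only that it may, and in part.

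**Repeat events.** A reader might also infer that the chi-square treats several events in one participant as independent. Section 6.3 does not define the counting unit. It places adverse outcomes next to the number lost to follow-up, which counts participants, so that charge is not established.

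**The primary result is untouched.** This is true. The IBD-Q comparison does not depend on adverse-event capture.

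**Conclusion.** The point holds as a weakness in the planned between-arm safety comparison. The only adverse-event form described is the WBV session form, nothing matching is described for control, and the two arms are then compared by a formal test. The result may show an excess under WBV that partly reflects closer observation, chiefly for mild, non-serious events.

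If the true risk is 20% to 30% in both arms and WBV capture is complete, false significance rises from the nominal 5% to about 18% to 27% at 70% control capture, and to 44% to 66% at 50%. At 10% risk the corresponding figures are about 10% and 22%. All of this rests on assumed risks and capture shares. If the sponsor's procedures already provide equal collection in both arms, the bias disappears and the protocol needs only to say so. The change should be made, but the primary conclusion does not depend on it.

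**What to change.** 1. Ask one identically worded adverse-event question once a week in both arms, at one designated WBV visit per week and at the control Zoom session, and again at the exit visit.
2. Add the question to the exit form, the WBV form and a short form for the Zoom session, and add adverse events to the data list in Section 6.1.
3. In Section 6.3, define the tested quantity as the number of participants with at least one event reported to these matched questions. This also fixes the counting unit.
4. Report further events noted at the other WBV sessions descriptively, for that arm only.

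The cost is one question at contacts that already take place and one REDCap field, with no added visits. The price in information is that mild events noted only at the other WBV sessions are left out of the formal test, though they are still reported. If some participants have already completed the six weeks, they will have no matched answers and should be shown separately.

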## Record Retention and Archiving

During the course of research, all records are the responsibility of the CI and are kept in secure conditions. The completed paper forms with non participant identifiable data are kept with the CI in a locked filing cabinet behind ID card security doors. Medical information on CRFs are kept in locked cabinets in the Research Department in the NHS Trusts. The records are retained on a secure repository at the University of Hertfordshire. Any electronic data is kept in encrypted storage which is password protected. When the research trial is complete, records are kept for a minimum of 5 years as per standards of GCP.

**Compliance**

The CI will ensure that the trial is conducted in compliance with the principles of the Declaration of Helsinki (1996), and in accordance with all applicable regulatory requirements including but not limited to the Research Governance Framework, Trust and Research Office policies and procedures and any subsequent amendments.

**12. Publication and Dissemination**

The findings will be written up in journal publications and evidence briefings and presented at various forums and conferences. Findings will importantly be reported back to patients across the UK via networks such as Crohn's and Colitis Foundation, healthcare professionals and a wider audience.
